The AMPK pathway may hold the key to answering these highly significant questions. AMPK not only plays a large role in global energy balance^12^ but also has a liver-specific role in de novo lipogenesis and fatty acid oxidation. AMPK activity is abnormally low in individuals with MASLD and is partly responsible for the accumulation of excessive amounts of liver fat.^4^ Importantly, exercise is a powerful activator of AMPK. Preclinical models show exercise changes the liver-specific AMPK pathway, leading to less liver fat accumulation mediated by reducing lipogenesis and increasing fatty acid oxidation.^13^ Interestingly, exercise-induced AMPK activation appears dose-related for several reasons: One, as exercise intensity and duration increase and ATP usage increases to the point where it cannot be regenerated quickly enough, AMPK becomes activated.^14^ The greatest AMPK activation is observed with longer durations and greater intensities of exercise.^15^ Two, in order to generate additional ATP during exercise, AMPK is released from glycogen, which is the main energy substrate used during sustained aerobic exercise, leading to AMPK activation (glycogen-bound AMPK is inactive).^16^ AMPK also regulates HSCs and, when stimulated by exercise, may inactivate HSCs and, in effect, prevent liver fibrogenesis.^17^

Prior studies in a small number of individuals with MASH demonstrated that exercise training improved downstream targets of AMPK^18,19^ and that only those individuals with MASLD who performed guideline-based amounts of aerobic exercise, defined as 750 metabolic equivalents of task (MET)-min/wk, achieved clinically meaningful improvement in intermediate biomarkers of liver fibroinflammation.^10^

Accordingly, through the conduct of the NASH AMP-activated protein kinase Exercise Dosing (AMPED) study, we aim to better understand the dose required and mechanisms to explain how exercise impacts clinical endpoints in MASH. We hypothesize that exercise training will deplete liver glycogen through activation of AMPK and improve biomarkers of liver fibroinflammation and liver histology in adults with MASH (Figure 1). If the anticipated results are achieved, we expect to change clinical practice and revolutionize how exercise training programs are delivered to individuals with MASLD, offering earlier intervention that may arrest, reverse, or even cure this leading cause of chronic liver disease.

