### Randomization

Subjects for the AMPED study are randomized 1:1:1 to arm 1 (750 MET-min/wk), arm 2 (1000 MET-min/wk), or arm 3 (SOC) for 16 weeks. To account for potential confounding from diabetes,^26^ stratified randomization has been invoked to ensure equal subjects in each group within the nondiabetes and diabetes stratum. Randomization is automatically performed by the study database (REDCap, Vanderbilt University), a secure, web-based application that supports data capture for research studies and serves as a data repository.^27^

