### Covariates

AMPED study participants directly report, or study staff verify self-reported information in the electronic health record documenting their demographics (eg, age, gender, race/ethnicity, education). Past medical, surgical, and social history are reviewed, including smoking status and history of illicit drug use. Medications are also reviewed both from self-report and the electronic health record, including those that are prescribed to treat MASH. Table 3 summarizes captured outcomes and covariates.

**TABLE 3 T3:** Study objectives and end points

End point	Methods
Primary efficacy	
Liver fat	• MRI-PDFF will assess change in liver fat after week 16
Secondary efficacy—key	
Liver and muscle glycogen	• MR-S will assess change in liver and muscle glycogen after week 16
Liver fat and liver stiffness using imaging analysis	• VCTE will assess change in liver fat and stiffness after week 16
Clinically meaningful improvement in liver fat and stiffness	• Proportion of participants with ≥26% relative reduction in VCTE-measured liver stiffness (kPA) after week 16 • Proportion of participants with ≥30% relative reduction in MRI-PDFF after week 16
Circulating biomarkers of hepatic injury	• Change in ALT, AST, CK-18, CRP, IL-6 after week 16 • Proportion of participants with ≥17 IU/L decrease in ALT after week 16
Circulating biomarkers of liver fibrosis and fibrogenesis	• Change in ELF score, Fibrosis-4 index (FIB-4), NFS, PRO-C3, TIMP-1 after week 16
Secondary efficacy—other	
Lipid parameters	• Change in LDL, HDL, triglycerides after week 16
Biomarkers for MASLD comorbidities	• Change in Hemoglobin A1c, insulin, plasma glucose, HOMA-IR, McAuley Index, ASCVD, Framingham score after week 16
Body composition	• Change in total body fat, visceral adipose tissue, subcutaneous adipose tissue, and fat-free mass as measured by DXA after week 16 • Change in waist and hip circumference, skinfolds at weeks 4, 8, 12, 16
Dietary intake and physical activity	• Change in fitness tracker measured step counts, self-reported physical activity (IPAQ, DASI), self-reported dietary intake at weeks. 4, 8, 12, 16
Patient-reported outcomes	• Change in PROMIS after week 16
Adherence	• % of completed exercise sessions after week 16 • % who achieved a priori definition of adherence (>80% session completion) after week 16
Safety	

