### Exercise training (Arms 1 and 2)

American College of Sports Medicine (ACSM) Guidelines for Exercise Prescription,^52^ including the frequency, intensity, time and type principles, are being used to teach subjects how to perform moderate-intensity aerobic exercise training (40%–59% maximal heart rate). To ensure physiologic adaptation, we included a progressive lead-in period until the target exercise dose is reached by week 4 (Table 4). This successfully prevented injury in our previous exercise intervention in sedentary individuals with MASH.^11^ Aerobic exercise can be completed by walking, jogging, or with cardio equipment (eg, recumbent bike). To further prevent injury, each session includes a warm-up and cool-down with low intensity walking and dynamic stretches. The warm-up is 10 minutes in length and is composed of 5 minutes of walking at 30%–40% of maximal heart rate followed by 5 dynamic exercises including knee to chest, 10-yard lateral shuffle, bent over twist, calf sweeps, and leg swings. Each exercise session ends with a 5-minute cool down on the treadmill at 30%–40% of maximal heart rate.

**TABLE 4 T4:** Acclimation period of progressive exercise for W1–W4

Study arm (MET-min/wk)	Week 1	Week 2	Week 3	Week 4
Arm 1 (750)	300	450	600	750
Arm 2 (1000)	300	500	750	1000

Abbreviation: MET, metabolic equivalents of task.

The study exercise physiologist is revising the program as fitness changes; subjects progress in speed or difficulty to ensure correct exercise intensity. Every exercise session is directly supervised (either in-person or with A-V telehealth) by research staff with real-time heart rate monitoring. After each session, the completed exercise dose is calculated by intensity (METs) × frequency (1 session) × time (min). For example, a typical 45-minute session composed of (10-minute warm-up × 3.0 METS) + (30-minute brisk walking × 5.0 METs) + (5-minute cool down × 3.0 METs) =200 METs. From there, the study exercise physiologist can vary the frequency, intensity, time and type prescription to design the next session (Table 5). For example, if a subject only has 30 minutes, exercise intensity may be increased to slow jogging (6.0 METs) to progress toward the assigned dose. This format is repeated until the assigned summative weekly dose is achieved. At the conclusion of the 16 weeks intervention period, subjects develop a plan to continue to exercise after the trial ends with the assistance of the staff exercise physiologist.

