### Adherence to exercise intervention

Adherence is meticulously monitored through various means. Each exercise session is directly supervised, with real-time heart rate monitoring facilitated via the fitness activity tracker. Following each session, study personnel meticulously complete a tracking sheet, which is thoroughly reviewed and subsequently entered in the database. This includes both the minutes completed and the METs. The objective of this monitoring protocol is to attain a total exercise dose each week at the assigned amount. Additional exercise beyond the prescribed in-person sessions is prohibited by the study protocol. Compliance with this stipulation is monitored through remote activity tracking facilitated by fitness tracker devices, with data downloads enabling surveillance. In cases where a subject is suspected of engaging in additional exercise based on this data analysis, they undergo an interview with study personnel for verification. Subsequent re-education is provided as deemed necessary to uphold adherence to the study protocol.

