### Sample size and power calculations

We conservatively expect our 3 groups (SOC control vs. 750 MET-mins/wk vs. 1000 MET-mins/wk), to experience mean relative reductions in MRI-PDFF of −5%, −30%, and −40%, respectively, with a SD of 6% (30% or greater is considered clinically significant because this surrogates for histologic improvement).^56,57^ We based these assumptions on (1) our recent meta-analysis of 551 individuals with MASLD from 14 exercise-intervention studies for which −36% and −46% MRI-measured liver fat reduction was observed for 750 MET-min/wk, and 1000 MET-min/wk of exercise, respectively, alongside a +7% gain for SOC controls;^10^ and (2) our NASHFit Trial that found subjects who performed 750 MET-min/wk to experience a −30% reduction in MRI-PDFF compared to +11% for SOC control subjects.^11^ Lower doses of exercise were not chosen because <750 min/wk was found to have similar efficacy as SOC. Additionally, based on our previous experience, we also account for 20% of the subject drop-out in the power calculation, although we fully expect it to be much less.^58^ Based on pairwise comparisons with two-sided *t* tests in an ANCOVA setting, each with a significance level of 0.017 (Bonferroni correction), a sample size of 15 per group (total sample size=45) yields at least 90% statistical power for each pairwise comparison.

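### Adherence is defined by sessions completed, so the endpoint does not show whether the randomised MET-min doses were delivered

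*Protocol article*

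**What the plan says.** All references are to the protocol article.

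- **Randomization:** the arms differ by weekly dose. Participants are "randomized 1:1:1 to arm 1 (750 MET-min/wk), arm 2 (1000 MET-min/wk), or arm 3 (SOC) for 16 weeks".
- **Exercise training (Arms 1 and 2):** dose is computed after each session from METs and minutes, and the exercise physiologist may vary any element of the next session. "This format is repeated until the assigned summative weekly dose is achieved". Table 4 sets a ramp that reaches the target dose in week 4.
- **Table 5:** both arms may train on 3–5 days a week, for 22–45 minutes in arm 1 and 30–60 minutes in arm 2.
- **Adherence to exercise intervention:** minutes and METs go into the database for every session, and the target is dose: "The objective of this monitoring protocol is to attain a total exercise dose each week at the assigned amount".
- **Table 3 (under Covariates):** the only two adherence endpoints count sessions. One is the percentage "of completed exercise sessions after week 16"; the other is the percentage of participants "who achieved a priori definition of adherence (>80% session completion) after week 16".
- **Doses below 750:** the Introduction reports that only people performing "guideline-based amounts of aerobic exercise, defined as 750 metabolic equivalents of task (MET)-min/wk, achieved clinically meaningful improvement". The sample size section says: "Lower doses of exercise were not chosen because <750 min/wk was found to have similar efficacy as SOC".

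**The concern.** The treatment is a weekly quantity of MET-min, but the endpoint meant to show that it was received counts attendances. Because frequency, duration and intensity can all vary within an arm, a completed session has no fixed dose value. Table 3 therefore has no endpoint built on the quantity that was randomised, although the protocol collects that quantity and names it as the monitoring target.

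This matters because the trial asks which dose is needed. The limitations section says that the feasibility of 1000 MET-min/wk is not known and that a threshold might leave no dose relationship to find. If the two exercise arms give similar results, the reader must know whether 750 and 1000 were actually delivered and kept apart. Session completion cannot answer that.

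**Working it through.** **The plan's own figure.** The adherence definition has no derived number to reproduce. The stated power of at least 90% does reproduce. Inputs from the sample size section: 15 per arm with 20% dropout leaves 12; the smallest difference is 40 − 30 = 10 points; SD 6; two-sided level 0.017. The normal approximation gives 10 / (6 × √(2/12)) = 4.082; subtracting the critical value 2.387 leaves 1.695, so power is 0.955. With the t distribution, power is 0.923 (22 df) or 0.934 (31 df). Adherence does not enter this calculation.

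**Does completing every session fix the dose?** Formula: sessions per week × minutes × METs. Sessions and minutes come from Table 5. Intensity is assumed to be 5 METs throughout, the value the protocol uses for brisk walking in its worked session.

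- Arm 1, all sessions completed: from 3 × 22 × 5 = 330 to 5 × 45 × 5 = 1125 MET-min/wk.
- Arm 2, all sessions completed: from 3 × 30 × 5 = 450 to 5 × 60 × 5 = 1500 MET-min/wk.
- Arm 2 with five 30-minute sessions: 5 × 30 × 5 = 750, exactly arm 1's assigned dose. Over a range of 3 to 6 METs the same week gives 450 to 900.

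Every one of these weeks scores 100% session completion, and the ranges of the two arms overlap.

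**The reverse error.** Suppose five sessions were planned in arm 1 and the participant does three of 45 minutes at 6 METs, the protocol's slow-jogging value. Delivered dose is 3 × 45 × 6 = 810 MET-min, above the assigned 750, while session completion is 3/5 = 60%, below the cut-off. This assumes that the five planned sessions stay in the denominator; the article does not say how planned sessions are counted.

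**Assigned dose over 16 weeks (Table 4, then target dose in weeks 4–16, 13 weeks).**

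- Arm 1: 300 + 450 + 600 + 13 × 750 = 11,100, an average of 693.75 per week.
- Arm 2: 300 + 500 + 750 + 13 × 1000 = 14,550, an average of 909.4 per week.

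**What an 80% cut-off implies.**

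- In a target-dose week: 0.8 × 750 = 600 and 0.8 × 1000 = 800 MET-min. For session counts this assumes sessions of equal dose with no make-up. For a MET-min ratio it follows directly.
- Averaged over the ramp: 0.8 × 693.75 = 555 and 0.8 × 909.4 = 727.5.
- Gap between arms at equal 80% completion: 800 − 600 = 200, against 250 planned.

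**The case against.** The strongest reply is that the protocol controls dose by other means. Sessions are supervised with live heart-rate monitoring, dose is calculated each time, the next session is designed from the result, and sessions continue until the weekly total is reached. Extreme weeks such as those above should be uncommon. Adherence is listed among the other secondary endpoints, no analysis described in the article uses the 80% rule, and delivered dose could be reported from the database whatever Table 3 calls adherence. How planned sessions are counted may well be set out in a fuller document.

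Most of this stands, and it limits the consequence. It does not rescue the definition. The article prints an a priori definition, and that definition is in a different unit from the treatment. Good control during the trial is something the adherence endpoint should demonstrate, and a session count cannot.

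Two stronger readings are tempting but unsupported:

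- **That counting sessions is what lets an arm 1 participant at about 600 MET-min/wk, a dose the plan likens to SOC, pass as adherent.** The 600 comes from the 80% cut-off; an 80% rule in MET-min admits the same 600 and 800. The sentence on lower doses also prints min/wk. MET-min/wk is the likely meaning given the Introduction, but that is an interpretation.
- **That separation between adherent participants shrinks by 80%.** That sets arm 2 at 80% (800) against arm 1 at 100% (750), a gap of 50 against 250. At equal 80% completion the gap is 200, a 20% reduction.

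**Conclusion.** The mismatch holds. Both adherence endpoints in Table 3 count sessions, while the randomised factor, the per-session calculation and the monitoring target are all in MET-min. With every session completed, an arm 2 week can equal arm 1's assigned 750 MET-min (at an assumed 5 METs), and a week that meets the dose can fall below the 80% session rule. The size is illustrative: it shows what the definition permits, not what is expected under supervision.

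The intent-to-treat primary comparison and the stated power are untouched. The damage is confined to the adherence endpoint and to interpreting the dose contrast, where a threshold effect must be told apart from under-delivery of 1000 MET-min/wk. The cut-off is a separate question from the unit and needs its own justification. This should be corrected, but it does not threaten the trial's validity.

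**What to change.** - In Table 3, define adherence as delivered MET-min divided by assigned MET-min, with the Table 4 ramp in the denominator: 11,100 in arm 1 and 14,550 in arm 2 over 16 weeks.
- Make the distribution of this ratio by arm, together with the separation in delivered MET-min between arms, the main adherence summary. Keep session attendance as descriptive.
- If a percentage cut-off is kept, justify it against the statements on doses below 750 in the Introduction and the sample size section, and correct or confirm the unit printed there.
- Label any dose-response analysis on delivered MET-min as supportive and non-randomised.

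The cost is one redefined table row and one added summary. Minutes and METs are already recorded for each session, so no new data are needed, and the exercise prescription does not change.

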## STUDY INTERVENTIONS

The AMPED study is a 16-week randomized, controlled interventional trial designed to test the hypothesis that exercise training will deplete liver glycogen through activation of AMPK and improve biomarkers of liver fibroinflammation and liver histology in adults with MASH.

### Exercise training (Arms 1 and 2)

American College of Sports Medicine (ACSM) Guidelines for Exercise Prescription,^52^ including the frequency, intensity, time and type principles, are being used to teach subjects how to perform moderate-intensity aerobic exercise training (40%–59% maximal heart rate). To ensure physiologic adaptation, we included a progressive lead-in period until the target exercise dose is reached by week 4 (Table 4). This successfully prevented injury in our previous exercise intervention in sedentary individuals with MASH.^11^ Aerobic exercise can be completed by walking, jogging, or with cardio equipment (eg, recumbent bike). To further prevent injury, each session includes a warm-up and cool-down with low intensity walking and dynamic stretches. The warm-up is 10 minutes in length and is composed of 5 minutes of walking at 30%–40% of maximal heart rate followed by 5 dynamic exercises including knee to chest, 10-yard lateral shuffle, bent over twist, calf sweeps, and leg swings. Each exercise session ends with a 5-minute cool down on the treadmill at 30%–40% of maximal heart rate.

**TABLE 4 T4:** Acclimation period of progressive exercise for W1–W4

Study arm (MET-min/wk)	Week 1	Week 2	Week 3	Week 4
Arm 1 (750)	300	450	600	750
Arm 2 (1000)	300	500	750	1000

Abbreviation: MET, metabolic equivalents of task.

The study exercise physiologist is revising the program as fitness changes; subjects progress in speed or difficulty to ensure correct exercise intensity. Every exercise session is directly supervised (either in-person or with A-V telehealth) by research staff with real-time heart rate monitoring. After each session, the completed exercise dose is calculated by intensity (METs) × frequency (1 session) × time (min). For example, a typical 45-minute session composed of (10-minute warm-up × 3.0 METS) + (30-minute brisk walking × 5.0 METs) + (5-minute cool down × 3.0 METs) =200 METs. From there, the study exercise physiologist can vary the frequency, intensity, time and type prescription to design the next session (Table 5). For example, if a subject only has 30 minutes, exercise intensity may be increased to slow jogging (6.0 METs) to progress toward the assigned dose. This format is repeated until the assigned summative weekly dose is achieved. At the conclusion of the 16 weeks intervention period, subjects develop a plan to continue to exercise after the trial ends with the assistance of the staff exercise physiologist.

**TABLE 5 T5:** FITT prescription for each exercise study arm

Study arm (MET-min/wk)	Frequency (d)	Intensity	Time (min)	Type
Arm 1 (750)	3–5	Moderate-vigorous	22–45	Aerobic
Arm 2 (1000)	3–5	Moderate-vigorous	30–60	Aerobic

Abbreviation: MET, metabolic equivalents of task.

### SOC (arm 3)

This group is receiving the best MASH clinical practices in accordance with practice guidelines.^53^ Because in-office hepatology counseling occurs every 12–24 weeks,^54^ standard counseling is happening at baseline and end-of-trial and is reinforced by American Liver Foundation handouts. This counseling includes information about completing at least 150 min/wk of physical activity as recommended by the ACSM.^8^ Physical activity is being measured remotely by fitness activity trackers like that in arms 1 and 2. Subjects randomized to SOC are given 16 weeks of fitness center membership and access to the study exercise physiologist for training sessions following completion of the study protocol.

### Dietary counseling

All subjects (arms 1–3) receive dietary counseling every 4 weeks per best clinical practices.^55^ A study Registered Dietitian will review food logs and provide energy expenditure goal-informed feedback. Exclusion of MASLD-promoting components (eg, beverages high in added fructose) is being reinforced. Macronutrient composition is being adjusted according to the Mediterranean diet.

### Adherence to exercise intervention

Adherence is meticulously monitored through various means. Each exercise session is directly supervised, with real-time heart rate monitoring facilitated via the fitness activity tracker. Following each session, study personnel meticulously complete a tracking sheet, which is thoroughly reviewed and subsequently entered in the database. This includes both the minutes completed and the METs. The objective of this monitoring protocol is to attain a total exercise dose each week at the assigned amount. Additional exercise beyond the prescribed in-person sessions is prohibited by the study protocol. Compliance with this stipulation is monitored through remote activity tracking facilitated by fitness tracker devices, with data downloads enabling surveillance. In cases where a subject is suspected of engaging in additional exercise based on this data analysis, they undergo an interview with study personnel for verification. Subsequent re-education is provided as deemed necessary to uphold adherence to the study protocol.

### Sample size and power calculations

We conservatively expect our 3 groups (SOC control vs. 750 MET-mins/wk vs. 1000 MET-mins/wk), to experience mean relative reductions in MRI-PDFF of −5%, −30%, and −40%, respectively, with a SD of 6% (30% or greater is considered clinically significant because this surrogates for histologic improvement).^56,57^ We based these assumptions on (1) our recent meta-analysis of 551 individuals with MASLD from 14 exercise-intervention studies for which −36% and −46% MRI-measured liver fat reduction was observed for 750 MET-min/wk, and 1000 MET-min/wk of exercise, respectively, alongside a +7% gain for SOC controls;^10^ and (2) our NASHFit Trial that found subjects who performed 750 MET-min/wk to experience a −30% reduction in MRI-PDFF compared to +11% for SOC control subjects.^11^ Lower doses of exercise were not chosen because <750 min/wk was found to have similar efficacy as SOC. Additionally, based on our previous experience, we also account for 20% of the subject drop-out in the power calculation, although we fully expect it to be much less.^58^ Based on pairwise comparisons with two-sided *t* tests in an ANCOVA setting, each with a significance level of 0.017 (Bonferroni correction), a sample size of 15 per group (total sample size=45) yields at least 90% statistical power for each pairwise comparison.

